### Outcomes

The primary composite endpoint is the cumulative incidence of reoperation and/or percutaneous drainage placement by the 30th postoperative day.

Secondary endpoints are as follows:
Incidence, severity, and time to diagnosis of anastomotic and duodenal leakLength of hospital stayOverall 30 days morbidity or in hospital if longer than 30 daysOverall 90 days mortality30 days readmission rate

Length of hospital stay is considered from the day of operation until discharge at home or at other facilities, or death. Postoperative complications, including anastomotic and duodenal leak, are classified according to the International Consensus on a Complications List After Gastrectomy for Cancer [23] and stratified by severity using the Clavien-Dindo classification [24].

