#### Postoperative procedure

All patients follow the usual postoperative pathway of each participating center except for abdominal drain management. Prophylactic drain in group A patients is daily evaluated checking for suspicious debt. In patients with a normal debt, a methylene blue test (the patient is asked to drink 200 ml of water/tea with 5 ml of methylene blue) is performed on postoperative day (POD) 4 and the test is considered negative if no blue staining of drain output is apparent within 60 min (the 200-ml colored solution stays in the esophageal/gastric lumen and this is considered as an indirect sign of the absence of an anastomotic leak). After the blue test is confirmed as negative, the drain can be removed. Each center is allowed to remove drain on whatever POD after a negative test. Drain management in patients with a suspicious debt or positive blue test is left to center preference (no further blue tests are planned). Postoperative complications are recorded until POD 30 or in hospital if hospital stay is longer than 30 days.

Reoperation under general anesthesia and/or percutaneous abdominal/thoracic drain placement during the first 30 PODs for any cause related to the previous gastrectomy is considered as an event in both groups. The cause-effect relationship decision is left to the lead site surgeon and in case of doubt, the investigator can ask for support from the steering committee. This specification was considered mainly necessary in case of unrelated pathology acquired after discharge but within POD 30 (e.g., operation for road accident). After discharge, patients are evaluated in the outpatient clinic on POD 30 or in the subsequent week. Follow-up calls are conducted by authorized medical or nursing staff at POD 60 ± 7 and 90 (max + 7 days) in order to assess patient’s clinical status.

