### Statistical methods

#### Analysis population

The primary analysis will be performed on a modified Intention-To-Treat (mITT) population, including all randomized patients who have undergone gastrectomy. Patients will be analyzed according to the treatment assigned at pre-operative randomization.

A secondary analysis will be performed on the As-Treated Population, including the same patients enclosed in the mITT population, classified according to whether they actually underwent the prophylactic drain placement or not.

Another secondary analysis will be carried out on the Per-Protocol (PP) population, including only patients undergoing surgery according to the arm assigned at randomization, and followed-up for at least 30 days. Also, patients dying before 30 days will be considered for the PP analysis.

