#### Statistical analysis

Categorical variables will be presented as absolute and percent frequencies, continuous variables as mean and standard deviation when approximately symmetrically distributed, and as median and interquartile range otherwise.

The proportion of patients undergoing re-intervention or percutaneous drain placement (primary endpoint) will be computed for each group. The difference between the primary end-point proportion in the treated group and in the control group will be computed with the corresponding confidence interval. If the upper limit of the 90% confidence interval of this proportion does not exceed the non-inferiority margin difference of 3.56%, the null hypothesis of inferiority will be rejected.

Further statistical analysis on the primary endpoint will follow a hierarchical approach: if the non-inferiority null hypothesis will be rejected, significance of differences in the primary endpoint between control and experimental arms will be further investigated with a Fisher’s exact test. The relation between the primary endpoint and treatment (drain placement or avoidance) will be further investigated using a multivariable Firth’s logistic model, adjusting for center, sex, age, tumor stage, and type of gastrectomy (total/subtotal).

To evaluate significance of differences between control and experimental arms, Fisher’s exact test or chi-square test will be used for nominal variables (reoperation, placement of additional percutaneous drain, anastomotic or duodenal stump fistula, postoperative mortality, hospital readmission), Wilcoxon-Mann-Whitney test for ordinal variables (fistula or complication severity), and *t* test (or the corresponding non-parametric test) for continuous variables (length of hospital stay, time from surgery to fistula detection). Statistical significance for secondary analyses will be set at *p* < 0.05 and statistical tests will be two-sided.

Statistical analyses will be performed using Stata®/IC 16.0 for windows (StataCorp LLC, College Station, TX, USA).

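### Death by postoperative day 30 without reintervention scores as event-free, and death ends length of stay, so both comparisons favour whichever arm has more such deaths

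*Protocol article*

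**What the plan says.** In the protocol article, Outcomes defines the endpoint by procedures alone: "The primary composite endpoint is the cumulative incidence of reoperation and/or percutaneous drainage placement by the 30th postoperative day". Postoperative procedure gives the event rule, again without death: "Reoperation under general anesthesia and/or percutaneous abdominal/thoracic drain placement during the first 30 PODs for any cause related to the previous gastrectomy".

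Statistical analysis fixes the estimator: "The proportion of patients undergoing re-intervention or percutaneous drain placement (primary endpoint) will be computed for each group". Analysis population fixes the denominator, a "modified Intention-To-Treat (mITT) population, including all randomized patients who have undergone gastrectomy". For the per-protocol set, which otherwise needs 30 days of follow-up, it adds: "Also, patients dying before 30 days will be considered for the PP analysis". It does not say that those patients count as events.

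For length of stay, Outcomes states: "Length of hospital stay is considered from the day of operation until discharge at home or at other facilities, or death". Statistical analysis compares it by t test "or the corresponding non-parametric test) for continuous variables (length of hospital stay, time from surgery to fistula detection".

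Mortality at 90 days is a separate secondary endpoint. The Abstract lists mortality among the endpoints assessed for superiority.

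**The concern.** Background and rationale presents the drain as a means of finding and treating leaks early. A plausible harm of omitting it is a leak recognised late. A patient who dies of such a leak before a reoperation or drain has had the worst outcome, yet adds one to the denominator and nothing to the numerator. In length of stay, the same patient looks like an early discharge.

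Under Objectives, rejecting inferiority would favour leaving the drain out. If deaths without reintervention were more common in that arm, the primary comparison would look better than the patients' outcomes warrant, and so would length of stay.

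**Working it through.** **1. The plan's own figure.** Sample size gives control 6.44%, no-drain 4.16% under the alternative, margin 3.56 points, one-sided alpha 5%, power 80% and 182 per arm. The Fig. 3 legend gives the unpooled Z test.

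- Variance sum: 0.0644×0.9356 + 0.0416×0.9584 = 0.1001.
- Distance: 0.0356 + (0.0644 − 0.0416) = 0.0584.
- n = (1.645 + 0.842)² × 0.1001 / 0.0584² = 181.5, so 182 per arm. Power at 182 is 80.1%.

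The plan's figure is reproduced. The sample size is correct for the endpoint as defined.

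**2. How a death without reintervention is scored.** The event rule requires a procedure, the estimator is a proportion, and the denominator includes everyone who had gastrectomy. Such a patient is in the denominator and not in the numerator. Deaths after a reintervention do count as events, so only deaths without one are affected.

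**3. Possible size in the primary comparison (illustration).** The article gives no rate of death without reintervention, so the rates here are assumptions. Suppose reintervention or death is 6.44% with a drain and 10% without, exactly at the margin. Let d points of the 10% be deaths without reintervention, with none in the drain arm. The scored no-drain rate is then 0.10 − d, and

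P(declare non-inferiority) = Φ(d/SE − 1.645), with SE = √[(0.0644×0.9356 + p(1 − p))/182] and p = 0.10 − d.

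| d | SE | d/SE | Probability |
|---|---|---|---|
| 0 | 0.02873 | 0 | 5.0% |
| 1 point | 0.02795 | 0.358 | 9.9% |
| 2 points | 0.02712 | 0.737 | 18.2% |

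One point of 182 is about 2 patients. The whole margin is 0.0356 × 182 = 6.5 patients.

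The same mechanism in counts: 12 drain and 8 no-drain reinterventions among 182 per arm give an upper 90% limit of +1.73 points, which passes. Adding 2 drain and 6 no-drain deaths without reintervention as events makes it 14 versus 14, with an upper limit of +4.59 points, which does not pass.

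**4. Power when deaths are counted.** Keep the planned reintervention rates, add the same proportion q to both arms, and use 182 per arm and 3.56 points. The distance stays at 0.0584 but the variance grows.

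| q in both arms | SE | Power |
|---|---|---|
| 0 | 0.02345 | 80.1% |
| 1% | 0.02544 | 74.2% |
| 2% | 0.02724 | 69.1% |
| 3% | 0.02890 | 64.7% |

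**5. Length of stay.** If a proportion q of an arm dies on day 5 instead of staying 30 days (both assumed), that arm's mean falls by q × (30 − 5): 0.5 days at 2% and 1.0 day at 4%. At an assumed in-hospital mortality of 2–4%, 0.02 × 182 = 3.6 to 0.04 × 182 = 7.3, so about 4–7 patients per arm die in hospital. That is an upper bound on short stays due to death, because a late in-hospital death is a long stay.

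**The case against.** The endpoint matches the stated aim. Objectives asks whether omitting the drain increases invasive procedures, and leaving death out of the composite is a legitimate design choice. This stands, and it is why the primary endpoint should not be replaced.

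Mortality is not ignored: it is a named 90-day endpoint with a between-arm test, so an excess would be reported. This also stands. But that is a superiority test and plays no part in the non-inferiority decision.

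Sensitivity analyses are commonly left to a statistical analysis plan, which is not shown here. That is a fair limit on the remedy. The scoring of deaths and the length-of-stay definition, however, are fixed in this article.

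A reader might infer from the 10% and 18% that the trial's type I error is inflated. The documents do not support that. The margin is 10% minus a control rate built from reoperations and additional drains only, so the figures describe a different outcome set against a borrowed margin, with every death without reintervention placed in one arm.

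A reader might also infer that a single unscored death is unusually decisive. With 12 drain-arm events among 182 per arm, 10 no-drain events pass (upper limit 3.01 points) and 11 fail (3.65). That is only what any binary rule does at its cut-off, and at the planned 202 per arm the step moves to 11 and 12.

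**Conclusion.** The point holds in conditional form. As written, death by POD 30 without reintervention is a non-event, and an early in-hospital death is a short stay. Both comparisons are biased towards the no-drain arm if it has more such deaths and towards the drain arm if that arm has more. Equal rates give no directional bias.

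The size cannot be fixed from the article. The 10% and 18% rest on the assumed rates, on all such deaths falling in the no-drain arm, and on applying 3.56 points to an outcome for which it was not derived. Nothing in the article shows that the no-drain arm will have more such deaths, so a claim that the trial is biased towards non-inferiority would go too far.

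**What to change.** Keep the primary endpoint, margin and sample size. Then:

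- **Primary endpoint.** Prespecify a supportive sensitivity analysis that counts death by POD 30 without prior reintervention as an event. Report its difference and 90% confidence interval beside the primary result. State that the 3.56-point margin was derived for procedures only, and that power against it falls to about 74%, 69% or 65% if 1%, 2% or 3% of both arms die without reintervention. Failing the margin in this analysis would then not by itself be read as harm.
- **Length of stay.** Give in-hospital deaths the worst rank in the Wilcoxon test, or analyse time to discharge alive with death as a competing event.

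The cost is a few sentences of analysis text and the lower power of the supportive analysis. No new data are needed, since mortality is already followed to day 90.

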### Participant timeline

The timeline of study events is displayed in Figs. 1 and 2. After a patient’s inclusion, a medical authorized staff member randomizes the participant using an online secure module on the International Gastrectomy Complications Database website (www.gastrodata.org), the day before the operation. Upon filling out the randomization form, an immediate reply is obtained, containing the study group. “Group A” includes patients with prophylactic drain placed at the end of the operation, “group B” includes patients without any abdominal drain at the end of the operation. The ratio 1:1 is obtained using a computer-generated randomization scheme, equally stratified (1:1 ratio) for type of operation (STG or TG). Enrollment type is competitive and is capped by type of surgery.

**Fig. 1 Fig1:**
[figure not shown]
Table of assessments

**Fig. 2 Fig2:**
[figure not shown]
Detailed schedule of outcomes assessments

### Sample size

According to a systematic review published in May 2020 [8], the cumulative incidence of reoperation in two RCTs was 7/115 = 6.1% (95% CI 2.5–12.1%) in the drain group and 3/115 = 2.6% (95% CI 0.5–7.4%) in the no drain group. Cumulative incidence of additional drain was 1/86 = 1.2% (95% CI 0.03–6.3%) in the drainage group and 2/84 = 2.4% (95% CI 0.3–8.3%) in the no drain group. Assuming a 70% of overlap between the two procedures in the drain group, the estimated proportion of the composite outcome is 6.44%, while assuming a 35% overlap in the no drain group, the estimated proportion of the composite outcome is 4.16%.

Hence, we assumed a reference group proportion of 6.44%, and a treated group proportion of 10% under the null hypothesis of inferiority and 4.16% under the alternative hypothesis of non-inferiority. A sample size of 182 in each group, corresponding to 364 patients overall, achieves 80% power to detect a non-inferiority margin difference between the group proportions of 3.56% (= 10–6.44%), with a one-sided significance level of 5%. A power curve for treated group proportion ranging from 3 to 7% under the alternative hypothesis of non-inferiority is presented in Fig. 3.

**Fig. 3 Fig3:**
[figure not shown]
Power curve as a function of treated group proportion ranging from 3 to 7% under the alternative hypothesis of non-inferiority. P0 (proportion in the control group) = 6.4%; alpha = 0.05; n1 = n2 = 182; P1.0 (proportion in the treated group under the null hypothesis of inferiority) = 10%. The test statistic used is the one-sided *Z* test (unpooled)

Considering a 10% dropout rate, 404 patients (202 in each group) are needed. In order to have a balanced percentage between total and subtotal gastrectomy, recruitment will end at 202 patients for each type of gastrectomy.

### Assignment of interventions

#### Sequence generation and concealment mechanism

Randomization plan has been generated using www.randomization.com program, and no one of the investigators has access to the list. Participants are randomized in a 1:1 ratio, using a secure web-based randomization system to receive either intervention or routine care, stratified by type of gastrectomy.

#### Blinding

The leading surgeon and the patient are blinded to the arm assigned until gastrointestinal reconstruction is completed (and anastomosis integrity test is done, if applicable). Before discovering the arm assigned, the surgeon will decide whether the patient meet or not the dropout criteria. There is no blinding for the patient, care providers, or coordinating researcher after the operation.

### Data collection and management

All study-related information will be stored securely at each participating center. Patient’s information will be stored in locked file cabinets in areas with limited access. Digital files are kept in password-protected applications.

A section on the www.gastrodata.org secure web-based platform was developed by a specialized software firm (www.Fluxedo.com) to facilitate multicenter data collection. All data, including center, surgeon, and patient data, are strictly anonymous and managed through secure codes. Cloud servers are compliant with the General Data Protection Regulation. An SSL certificate is installed to encrypt data exchanged between applicative and users. Dataset and applicative are accessible only with personal credentials owned by authorized investigators. Each participating center has access only to its own dataset.

Data are collected until POD 91. Before recruitment process starts, investigators from each participating center will practice with the leading center data manager in order to increase proficiency in data entry and regular audits will be held with all participating centers.

Anonymization was guaranteed by removing personally direct identifiers from the dataset (e.g., using age instead of date of birth) and recoding indirect identifiers when considered at risk for a possible identification.

### Statistical methods

#### Analysis population

The primary analysis will be performed on a modified Intention-To-Treat (mITT) population, including all randomized patients who have undergone gastrectomy. Patients will be analyzed according to the treatment assigned at pre-operative randomization.

A secondary analysis will be performed on the As-Treated Population, including the same patients enclosed in the mITT population, classified according to whether they actually underwent the prophylactic drain placement or not.

Another secondary analysis will be carried out on the Per-Protocol (PP) population, including only patients undergoing surgery according to the arm assigned at randomization, and followed-up for at least 30 days. Also, patients dying before 30 days will be considered for the PP analysis.

#### Statistical analysis

Categorical variables will be presented as absolute and percent frequencies, continuous variables as mean and standard deviation when approximately symmetrically distributed, and as median and interquartile range otherwise.

The proportion of patients undergoing re-intervention or percutaneous drain placement (primary endpoint) will be computed for each group. The difference between the primary end-point proportion in the treated group and in the control group will be computed with the corresponding confidence interval. If the upper limit of the 90% confidence interval of this proportion does not exceed the non-inferiority margin difference of 3.56%, the null hypothesis of inferiority will be rejected.

Further statistical analysis on the primary endpoint will follow a hierarchical approach: if the non-inferiority null hypothesis will be rejected, significance of differences in the primary endpoint between control and experimental arms will be further investigated with a Fisher’s exact test. The relation between the primary endpoint and treatment (drain placement or avoidance) will be further investigated using a multivariable Firth’s logistic model, adjusting for center, sex, age, tumor stage, and type of gastrectomy (total/subtotal).

To evaluate significance of differences between control and experimental arms, Fisher’s exact test or chi-square test will be used for nominal variables (reoperation, placement of additional percutaneous drain, anastomotic or duodenal stump fistula, postoperative mortality, hospital readmission), Wilcoxon-Mann-Whitney test for ordinal variables (fistula or complication severity), and *t* test (or the corresponding non-parametric test) for continuous variables (length of hospital stay, time from surgery to fistula detection). Statistical significance for secondary analyses will be set at *p* < 0.05 and statistical tests will be two-sided.

Statistical analyses will be performed using Stata®/IC 16.0 for windows (StataCorp LLC, College Station, TX, USA).

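### The primary non-inferiority comparison leaves out the randomisation stratum and names no interval method; a stratified score interval would be a minor, cheap improvement

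*Protocol article*

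**What the plan says.** All references are to the protocol article.

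- **Design.** Under Sequence generation and concealment mechanism, allocation is 1:1 and "stratified by type of gastrectomy". The Sample size section closes recruitment at 202 patients for each type of gastrectomy.
- **Primary comparison.** Under Statistical analysis: "The difference between the primary end-point proportion in the treated group and in the control group will be computed with the corresponding confidence interval". The rule follows: "If the upper limit of the 90% confidence interval of this proportion does not exceed the non-inferiority margin difference of 3.56"%, inferiority is rejected. Neither the stratum nor a method for the interval is mentioned.
- **Where the stratum is used.** The same section includes type of gastrectomy, with center, sex, age and tumor stage, in a multivariable Firth logistic model that further investigates the primary endpoint.
- **Planning.** The Sample size section takes 6.44% for the drain arm and, for the no-drain arm, "a treated group proportion of 10% under the null hypothesis of inferiority and 4.16% under the alternative hypothesis of non-inferiority". It works "with a one-sided significance level of 5"%. On this basis 182 per group "achieves 80% power to detect a non-inferiority margin difference between the group proportions of 3.56% (= 10–6.44"%). The legend of Fig. 3 adds: "The test statistic used is the one-sided" Z test, unpooled. That legend is the only place where a test statistic for the non-inferiority comparison is named, and it concerns the power curve.

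**The concern.** There are two separate points, and they should not be added together.

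First, an analysis normally respects the factor by which patients were allocated. Here the number that decides the trial ignores it. The model that includes it works on the odds scale, so it cannot answer the non-inferiority question, which is set as a difference of 3.56 percentage points. At stake are agreement between design and analysis, and a little precision.

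Second, the choice of interval for a risk difference matters when events are few. With 182 per arm the planned rates imply about 11.7 control events (182 × 0.0644). In the experimental arm they imply about 7.6 events under the alternative (182 × 0.0416) and 18.2 at the null (182 × 0.10). The unpooled normal interval tends to be too short in this range. If it were carried over from the power calculation, the one-sided 5% error rate would be slightly exceeded, and some plausible results would be declared non-inferior that a score interval would not.

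**Working it through.** **1. Reproducing the stated sample size.** Inputs from the Sample size section: control 0.0644, experimental 0.0416, margin 0.0356, one-sided alpha 0.05, power 0.80. With unpooled variance:

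n per arm = [pc(1−pc) + pt(1−pt)] × (1.645 + 0.842)² / (margin + pc − pt)²
= (0.06025 + 0.03987) × 6.183 / 0.0584²
= 0.10012 × 6.183 / 0.003411 = 181.5, rounded up to 182.

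This matches the stated 182 per arm and 364 in total. Approximate power at 182 is 80.1%. Allowing for dropout, 364 / 0.9 = 404.4, against the stated 404. The unpooled Z is therefore confirmed as the planning basis.

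**2. Effect of leaving out the stratum.** Stratum event rates are not in the documents, so these are assumptions: two equal strata, control rates averaging 6.44%, and a difference of 3.56 points in each (the null boundary). The crude variance, per arm size, is 0.0644 × 0.9356 + 0.10 × 0.90 = 0.15025. The within-stratum variance is the average over strata of the same expression.

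| Control rates in the two strata | Within-stratum variance | Crude SE / stratified SE | Nominal one-sided error of the crude analysis |
|---|---|---|---|
| 6.44% / 6.44% | 0.15025 | 1.000 | 5.0% |
| 4% / 8.88% | 0.14906 | 1.004 | 4.9% |
| 3% / 9.88% | 0.14789 | 1.008 | 4.9% |
| 2% / 10.88% | 0.14631 | 1.013 | 4.8% |

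The last column is 1 − Φ(1.645 × SE ratio). The effect is neutral to slightly conservative. In a simulation of the unpooled interval (1,000,000 replicates, stratum rates up to 3% / 9.88%), stratifying raised power by at most about 0.1 points at 182 per arm (81.6% to 81.7%) and 0.4 points at 202 (84.8% to 85.2%).

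**3. Effect of the interval method.** The rule (upper 90% limit no greater than 3.56%) was enumerated exactly over both binomial distributions, with the experimental rate set to the control rate plus 3.56 points. The analysis is unstratified.

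| Control rate | Unpooled Z, 182 per arm | Miettinen-Nurminen, 182 | Unpooled Z, 202 per arm | Miettinen-Nurminen, 202 |
|---|---|---|---|---|
| 2% | 6.68% | 4.26% | 6.54% | 4.62% |
| 3% | 6.35% | 4.50% | 5.99% | 4.59% |
| 4% | 5.96% | 4.72% | 5.79% | 4.66% |
| 5% | 5.65% | 4.84% | 5.56% | 4.79% |
| **6.44% (planned)** | **5.39%** | **4.91%** | **5.42%** | **4.97%** |
| 8% | 5.20% | 4.99% | 5.29% | 5.05% |
| 10% | 5.16% | 4.98% | 5.11% | 5.07% |

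Exact power at 6.44% v 4.16% is 81.5% (unpooled Z) and 78.3% (score) at 182 per arm, and 84.6% and 81.9% at 202.

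**4. A result on which the methods disagree.** Take 8 events in each arm of 182. The proportion is 8/182 = 0.04396 and the difference is 0. The unpooled SE is √(2 × 0.04396 × 0.95604 / 182) = 0.02149, so the upper limit is 1.645 × 0.02149 = 3.53%, and non-inferiority is declared. The Miettinen-Nurminen upper limit is 3.77%, and it is not. With 10 events in each arm of 202 the limits are 3.55% and 3.74%.

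**5. Are the two points linked?** No. Stratifying while keeping the unpooled variance left simulated error at 5.4 to 5.5%. The score interval corrects the error rate; stratification aligns the analysis with the design.

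**The case against.** A reader might infer that the plan commits itself to an unpooled (Wald) interval and so breaks its own 5% error rate. The documents do not support that. The unpooled Z is tied to the power curve only, and the Statistical analysis section leaves the interval open. A sample size from a normal approximation followed by a score interval would fit the text as written. The interval formula is also commonly left to a statistical analysis plan, which is not shown, so its absence here is not a fault. This part of the objection stands, and the error figures are conditional on the planning method being reused.

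A reader might also infer that ignoring the stratum threatens the error rate. It does not: the crude analysis is neutral to slightly conservative. The cap per type of gastrectomy was set for balance rather than precision, and the Firth model does adjust for the factor. All of this stands. What remains is that the crude difference is stated, not left open, and that the adjusted model is on a scale that cannot be compared with the margin.

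Finally, the larger error figures need control rates well below plan. At 8 to 10% the excess is only 0.1 to 0.3 points, and the Western studies in the Discussion point to higher rates (for example, 24.1% reoperation with drain in a total gastrectomy trial). Against that, the planning figure for reoperation with drain, 7/115, has a 95% interval reaching down to 2.5%. Both directions are open, so neither extreme should carry the point.

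**Conclusion.** The point holds as a minor improvement. The primary comparison ignores the factor used for stratified randomisation. The cost is a standard error 0 to 1.3% too large over the assumed stratum rates and a fraction of a point of power, with no inflation of error.

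The interval method is a separate and conditional matter. If the unpooled Z were used for the analysis, exact error would be 5.39% at 182 per arm and 5.42% at 202 under the planned 6.44% v 10%, an excess of about 0.4 points. It would be about 6% or more only at control rates of about 4% or lower. A score interval gives 4.91% and 4.97% at the planned rates. The choice can still decide the trial at realistic counts such as 8 v 8, and care is not blinded after the operation, so it is worth settling before the data are seen.

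The exact results assume independent binomial outcomes, equal analysed arms and no stratification. The stratum rates are assumptions throughout.

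**What to change.** State the primary analysis as the Mantel-Haenszel risk difference stratified by type of gastrectomy as randomised, with a 90% stratified Miettinen-Nurminen (score) interval whose upper limit is compared with 3.56%. Keep the crude difference as descriptive. If an analysis plan already names such an interval, confirming it is enough for that part. If only one element can be changed, the score interval is the one that affects the error rate.

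The cost is one sentence and a small change in the power to be quoted. From the unstratified score interval, exact power at the planned rates is 78.3% if 182 per arm are analysed and 81.9% at 202. The modified intention-to-treat set keeps every randomised patient who undergoes gastrectomy, so the analysed number may lie above 182.

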## Methods: Participants, interventions, and outcomes

### Study settings

All hospitals belonging to the GIRCG are eligible to participate in the ADiGe Trial, irrespective of their hospital volume. A total of 9 centers applied to participate, and, at the time of this publication, the study has already been approved by the local IRB of each center (Verona University Hospital, the leading Center, Orbassano Hospital of Turin, San Raffaele Hospital of Milan, Morgagni Hospital of Forlì, Federico II University Hospital of Naples, Niguarda Hospital of Milan, S. Orsola-Malpighi Hospital of Bologna, Parma University Hospital, Modena University Hospital).

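### Length of stay is compared by an unadjusted two-sample test although discharge pathways are centre-specific and centre is recorded; the test is valid, and the only loss is precision

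*Protocol article*

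**What the plan says.** The Statistical analysis section of the Protocol article assigns length of stay a t test "or the corresponding non-parametric test) for continuous variables (length of hospital stay, time from surgery to fistula detection". The significance level for secondary analyses is "< 0.05 and statistical tests will be two-sided". The Abstract lists stay among the secondary endpoints assessed for superiority, and the Outcomes section defines it: "Length of hospital stay is considered from the day of operation until discharge at home or at other facilities, or death".

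On care after surgery, the Postoperative procedure section says: "All patients follow the usual postoperative pathway of each participating center except for abdominal drain management". The day of drain removal is partly local as well: "Each center is allowed to remove drain on whatever POD after a negative test".

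On design, "A total of 9 centers applied to participate" (Study settings), and enrolment across them is competitive (Participant timeline). "Participants are randomized in a 1:1 ratio" (Sequence generation and concealment mechanism), "to receive either intervention or routine care, stratified by type of gastrectomy"; centre is not a stratification factor. Centre is recorded in the trial database (Data collection and management). In the Statistical analysis section, centre and type of gastrectomy are covariates only in the Firth logistic model of the primary endpoint.

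**The concern.** Stay depends partly on when a centre habitually discharges its patients, and this trial deliberately leaves that habit alone. Differences between centres can therefore form part of the variance of stay. An unadjusted test leaves that part in the error term, although centre is known at baseline, is already in the database, and is already judged worth adjusting for in another model. The same test ignores type of gastrectomy, the one factor on which randomisation is stratified.

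Stay matters to the argument for omitting drains. The Background cites a shorter stay as a possible benefit, and the Discussion quotes 18.8 against 12.9 days in the one Western randomised trial. At stake is how sharply this secondary comparison can be estimated.

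**Working it through.** **The plan's own figure.** The document sizes the trial for the primary endpoint only. With 6.44% in control, 4.16% in the experimental arm, a margin of 3.56%, one-sided alpha 5%, 80% power and unpooled variance:

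n per arm = (1.645 + 0.842)² × (0.0644 × 0.9356 + 0.0416 × 0.9584) / (0.0356 + 0.0228)² ≈ 6.18 × 0.1001 / 0.00341 ≈ 182.

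This reproduces the stated 182 per arm and 364 in total. Dividing by 0.9 gives 404.4, against the stated 404. No standard deviation, target difference or between-centre variance is given for stay.

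**Inputs for stay.** From the document: 182 evaluable patients per arm, 9 centres, two-sided 5%. Assumed: ρ, the share of the variance in stay (on the scale analysed) that lies between centres, taken from 2% to 30%.

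**Formulas**, in units of the total standard deviation of stay:

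- Unadjusted standard error = √(2/182) = 0.105.
- Difference detectable unadjusted with 80% power = (1.960 + 0.842) × 0.105 = 0.294.
- Centre-adjusted standard error = 0.105 × √(1 − ρ), so the interval narrows by 1 − √(1 − ρ).
- Adjusted power at the same difference = Φ(2.802/√(1 − ρ) − 1.960).
- Patients needed unadjusted to match 364 adjusted = 364/(1 − ρ).

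| ρ (assumed) | Interval narrower by | Power (80% unadjusted) | Patients to match 364 |
|---|---|---|---|
| 2% | 1% | 80.8% | 371 |
| 5% | 3% | 82.0% | 383 |
| 10% | 5% | 84.0% | 404 |
| 20% | 11% | 88.0% | 455 |
| 30% | 16% | 91.8% | 520 |

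**Cost of adjusting.** The table ignores it. Chance correlation between arm and the 8 centre terms uses up on average about 8/363 = 2.2% of the information, or about 1.1% on the standard error. That cancels the gain at ρ = 2% and about halves it at 5%.

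**Simulation check.** About 364 patients in 9 unequal centres (assumed 25% down to 5% of patients), randomisation not stratified by centre, true difference 0.294, 2,000 runs per scenario. Monte Carlo error near 80% power is √(0.8 × 0.2/2000) = 0.009. The linear columns use normal data, which corresponds to log stay; the rank columns use lognormal data.

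| ρ | t test | Linear model with centre | Wilcoxon | van Elteren |
|---|---|---|---|---|
| 0% | 0.79 | 0.78 | 0.78 | 0.76 |
| 5% | 0.81 | 0.81 | 0.78 | 0.78 |
| 10% | 0.79 | 0.84 | 0.78 | 0.80 |
| 20% | 0.80 | 0.87 | 0.78 | 0.84 |
| 30% | 0.80 | 0.89 | 0.77 | 0.89 |

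With no true difference, the unadjusted tests rejected in 4.4% to 5.7% of runs. Type of gastrectomy was not simulated. To the extent that it predicts stay and the scheme balances arms within each type, the unadjusted test errs on the conservative side.

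**The case against.** The strongest reply is that nothing here is wrong. Randomisation did not stratify by centre, so an unadjusted test agrees with the design in that respect and keeps its level. Stay is one of several secondary endpoints, does not appear in the Objectives section, and cannot change the non-inferiority conclusion. The other between-arm secondary tests, and the primary confidence interval as described, are unadjusted too. All of this stands, and it limits the importance of the point. It does not show the stated choice to be a good one for an outcome that local pathways can shape directly.

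The reply continues that the gain is wholly assumed. That also stands: the document shows that pathways may differ, not that discharge times do, and at ρ of 5% or less there is nothing worth having. If the rank test is used, as skewed stay would suggest, the simulated gain at 10% is only 0.78 to 0.80.

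Three stronger readings are tempting and not supported:

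- A reader might infer that the unadjusted comparison is biased or rejects too often. Neither follows, and the simulated error rates stay near 5%.
- A reader might count chance imbalance of centres between arms as a second harm. Its standard deviation is √ρ × 0.105, which is 0.033 at ρ = 10%, and it is already contained in the unadjusted standard error of 0.105. It is the same loss of precision.
- A reader might express the loss as extra patients on top of 404. The planned evaluable number is 364, and such figures hold for a linear model only.

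A full protocol or SAP may hold a supportive adjusted model. The article nevertheless states the test, so the point concerns a stated choice and not missing detail.

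**Conclusion.** The point holds as a modest matter of efficiency. The stated test for length of stay is valid, and the trial's primary conclusion does not depend on it. It leaves out a recorded baseline factor that may well influence stay, together with the stratification factor. The price is precision only: next to nothing if centre explains 5% or less of the variance, about 5% of the interval's width at 10%, and 11% to 16% at 20% to 30%. These sizes rest on assumed variance shares, on 182 evaluable patients per arm, and on a linear model on a suitable scale. For a rank test they are smaller at modest centre effects. The change is worth making because it costs little, not because the present analysis would mislead.

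**What to change.** In the Statistical analysis section, or in the SAP before any comparison by arm, name one of the following as the length-of-stay analysis:

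- a linear model on log stay with arm, centre and type of gastrectomy, reporting the adjusted ratio with its 95% confidence interval; or
- if a rank test is kept, a van Elteren test stratified by centre, and also by type of gastrectomy where cell sizes allow.

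Fix a rule for pooling small centres before analysis, and keep the unadjusted test as a sensitivity analysis.

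The cost is wording and a few lines of code, about 9 degrees of freedom (8 for centre, 1 for type of gastrectomy), and the pooling rule. If centre explains nothing, the adjusted analysis gives up a point or two of power at most (0.79 to 0.78 for the linear model, 0.78 to 0.76 for the rank test in the simulation). The log model also states the effect as a ratio of geometric means, which is a different quantity from a difference in mean days or a rank comparison. Neither option changes the fact that stay ends at death, so that an early death counts as a short stay; that is a separate question.
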